### Statistical methods

An intention-to-treat (ITT) and per-protocol analysis is planned. The data will be summarized using means with standard deviations and medians with inter-quartile range. Counts and percentages will be used to describe categorical measures. Baseline characteristics will be assessed to identify any differences between treatment groups that would require adjustment in subsequent analyses. A linear mixed effects model will be applied to assess treatment effects over time. Pairwise, post hoc comparisons will be made using the Student t-test. All tests will be two-tailed and assessed at the 5% alpha level.

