### Consent and randomization

Once eligible for the study, the participants will be provided with information about the study. After obtaining the informed consent, they will be randomized to either the intervention or the control group by the hospital pharmacist external to this project. We will be looking at the imaging (CT/MRI) to determine the type of stroke (Ischaemic vs Haemorrhagic) and there will be stratification within stroke types utilizing block permutation design. Rights of withdrawal without prejudice to future treatment at any time in the study will be emphasized.

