### Outcomes

Primary outcome include change inGait velocity/walking distance in GaitRite (Electronic walkway)

Secondary outcomes include changes inSpasticity measured by Modified Ashworth Scale (MAS)2 Min Walk Test [18]Berg Balance Score [19]Timed Up and Go (TUG) [20]Lower limb function by ABILICO [21]Goal Attainment Scale (GAS) [22]Quality of life by SF 12 (Rand version)ADL score -The Functional Autonomy Measurement System (SMAF) [23]Passive range of motion at the ankle joint.Use of ActivPAL to quantify ambulatory activities at home [25]

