### Procedures

Participants will undergo assessments at base line, 3 weeks, 3 months and 5 months following the injection (Fig. 1). All primary and secondary outcomes will be measured at all 4 time points. Additionally, the demographic and health characteristics such as age, gender, weight, type of stroke, affected side and mean time since stroke will he determined. A sensory evaluation will also be carried out in all the participants in the RCT.

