### Sample size calculation

In most of the RCT’s included in our systematic review sample inadequacies were identified. Chief among these was the problem of inadequate sample calculations for repeated measures design. In repeated measures studies, within patient observations are correlated which often results in an estimate of the standard deviation that is an underestimate of the true standard deviation. Failure to account for this leads to an increased in the risk of a Type 1 error. In this study, we inflated our sample size by applying a design effect (DEFF) of 1.5 to account for the repeated measure design. Calculations were based on the requirement that effects be detected at the 5% alpha level with 90% statistical power. Based on available evidence, it was assumed that the clinically meaningful difference between the two treatment groups would be 0.13 points in gait speed with a standard deviation of 0.13. Based on these assumptions, a sample of 35 patients per group is required following the application of the design effect (*n* = 23 * DEFF). We have further inflated the sample size to *n* = 47 per group to account for an expected attrition rate of 25%.

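### Adjustment covariates are to be chosen from observed baseline differences between randomised groups, which makes the primary model data-dependent and gives up precision that fixed covariates would supply

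*Protocol article*

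**What the plan says.** The Statistical methods section of the protocol article sets the covariate rule: "Baseline characteristics will be assessed to identify any differences between treatment groups that would require adjustment in subsequent analyses". It gives no threshold and names no covariate. The model follows: "A linear mixed effects model will be applied to assess treatment effects over time". Then: "Pairwise, post hoc comparisons will be made using the Student t-test".

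Three other sections bear on this:

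- **Consent and randomization** makes ischaemic versus haemorrhagic stroke the stratification factor: "there will be stratification within stroke types utilizing block permutation design". No section carries stroke type into the analysis.
- **Outcomes** words the primary endpoint as a change: "Primary outcome include change inGait velocity/walking distance in GaitRite (Electronic walkway".
- **Procedures** has baseline gait velocity measured in everyone: "All primary and secondary outcomes will be measured at all 4 time points", the first of these being baseline. No section says how that baseline value enters the model.

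**The concern.** If allocation is sound, any baseline difference between the arms is chance. Letting it decide the adjustment means the primary model is settled only after the data are seen. With no threshold given, what counts as a difference that calls for adjustment is open to judgement.

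The rule also looks at the wrong property. A covariate earns its place by predicting the outcome, not by happening to differ between arms. Baseline gait velocity, the obvious predictor of later gait velocity, would become a covariate only by accident. Stroke type is held near balance by the stratified blocks, so the rule would seldom pick it, although it is the factor the design singles out. The Student t-test takes neither a covariate nor a stratum.

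At stake are the precision of the gait velocity effect and the defence of the primary result as pre-specified. The article hopes that result will inform reimbursement.

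**Working it through.** **Inputs from the article.** Difference 0.13, SD 0.13, 90% power, design effect 1.5, 25% attrition (Sample size calculation); two-sided 5% tests (Statistical methods).

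**Assumed, because the article does not give them.** Correlation ρ between baseline and follow-up gait velocity; a 5% significance screen for baseline differences; the size of any stroke-type effect; the split of stroke types.

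**1. The plan's own figure.** n = 2(1.96 + 1.282)² × (0.13/0.13)² = 21.0, so 22 per group by the normal approximation. The exact t-test needs 22.02, so 23. Then 23 × 1.5 = 34.5, so 35; 35/0.75 = 46.7, so 47 per group and 94 in all. This reproduces the article.

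**2. What the rule would select.** Under a 5% screen, baseline gait velocity is selected in about 5% of trials, however prognostic it is. Procedures lists age, gender, weight, affected side and time since stroke besides stroke type. With baseline velocity that makes six candidates not held in balance by design. If they are treated as independent, the chance that at least one shows a difference is 1 − 0.95⁶ = 26%. Baseline values of the secondary outcomes would raise this.

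**3. Precision.** With equal variance σ² at both visits, the residual variance per patient is σ² for follow-up values alone, 2(1 − ρ)σ² for change, and (1 − ρ²)σ² with baseline as a covariate. The ratio of covariate to change analysis is (1 + ρ)/2; of covariate to follow-up analysis, 1 − ρ².

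| ρ (assumed) | Change | Baseline fixed | Variance cut vs change | Variance cut vs follow-up value |
|---|---|---|---|---|
| 0.5 | 1.00σ² | 0.75σ² | 25% | 25% |
| 0.7 | 0.60σ² | 0.51σ² | 15% | 49% |
| 0.8 | 0.40σ² | 0.36σ² | 10% | 64% |

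The standard error against change falls by 1 − √0.75 = 13%, 1 − √0.85 = 8% and 1 − √0.90 = 5%.

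With 35 per arm, σ = 0.13 and ρ = 0.7, the standard errors are:
- follow-up values: 0.13 × √(2/35) = 0.0311
- change: 0.0311 × √0.60 = 0.0241
- baseline fixed: 0.0311 × √0.51 = 0.0222

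**4. Are the error bars right?** This was simulated under no effect with 35 per arm, one follow-up visit, allocation balanced within two strata and 5,000 to 6,000 replicates per setting.

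- *Follow-up values, baseline added only if it differs at 5%, no stroke-type effect:* type I error 4.4%, 3.8% and 2.6% at ρ = 0.5, 0.7 and 0.85. At ρ = 0.7 the mean reported standard error is 0.0306 against a true 0.0287.
- *Change score:* type I error about 4.5% to 5.6%, with or without stroke type in the model, and 4.3% to 5.3% when the screen is applied.
- *Follow-up values, unadjusted, stroke type omitted (80/20 split):* type I error 4.4% to 5.1% if stroke types differ by 0.3 to 0.5 SD, and about 3.0% to 3.5% if they differ by 1 SD.

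**5. Power.** At the stated 0.13 with SD 0.13 and 35 per arm, every analysis exceeds 98%. At half that effect (0.065) and ρ = 0.7, power is 56% for follow-up values with the screen, 75% for change and 82% with baseline fixed.

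**The case against.** The best defence is that baseline may already be in the analysis. The outcome is worded as a change, and the model runs over time on data that include the baseline visit. A change score, or a mixed model with baseline as one of the responses, uses baseline whether or not it looks imbalanced. This stands, and it makes the 25%, 15% and 10% variance cuts the more relevant figures. It does not remove the point: the article does not say which form is meant, and the adjustment rule is data-driven under either.

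Second, a condensed article may leave its covariate list to an analysis plan. The absence of a list is indeed no fault. But the article does more than stay silent: it states how adjustment will be decided, and an analysis plan that fixed the covariates in advance would contradict it.

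Third, no test or threshold is stated, so judgement about prognostic value might enter. That is fair as to the 5% screen, which is an assumption here. But the rule still starts from observed differences, and the missing threshold leaves the choice more open.

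Fourth, nothing in the article says stroke type predicts gait speed. This also stands: leaving it out distorts the error rate noticeably only if the stroke types differ strongly, and only when follow-up values are compared.

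**Conclusion.** The point holds as one of pre-specification and precision. The stated rule makes the primary model depend on chance imbalance, and it is unlikely to select the stratification factor. Fixing baseline gait velocity would cut the variance of the treatment effect by about 25%, 15% or 10% against a change analysis, and by 25%, 49% or 64% against follow-up values without baseline. These figures rest on assumed correlations of 0.5, 0.7 and 0.8 and on equal variances at both visits.

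A reader might infer three stronger things that the article does not support:

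- *That the error bars are wrong in general.* They are about right on the change reading. On the follow-up reading they are too wide, which is conservative. No setting showed material inflation of false positives.
- *That the trial is underpowered as a result.* At its own 0.13 and 0.13, power exceeds 98% with 35 per arm under every analysis tried. The loss matters only if the true standardised effect is clearly smaller.
- *That the treatment estimate is biased.* This was not shown. The effect of choosing covariates by judgement, without a threshold, was not quantified.

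**What to change.** Replace the sentence on baseline differences with:

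*All models adjust for the baseline value of the outcome (for the primary, baseline gait velocity, as a covariate or as a constrained baseline response) and for stroke type, the randomisation stratum. Both are fixed in advance. Pairwise comparisons are contrasts from this model. Baseline tables are descriptive and do not determine adjustment.*

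The cost is a short change of wording, carried into the analysis plan if one exists. Both variables are already collected, and the model gives up only a couple of degrees of freedom. Sample size, visits and procedures do not change. Time since stroke, also collected, could be named in advance as a further covariate, but this is optional and the point does not depend on it.

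### Pairwise comparisons are assigned to the Student t-test, although contrasts from the mixed model already planned would keep more patients and carry the baseline adjustment

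*Protocol article*

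**What the plan says.** All from the protocol article.

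- **Statistical methods**, main analysis: "A linear mixed effects model will be applied to assess treatment effects over time". The next sentence reads: "Pairwise, post hoc comparisons will be made using the Student t-test". It does not say which pairs are meant, whether raw values or changes are compared, or whether the tests are contrasts from the model.
- **Statistical methods**, analysis sets, baseline and error level: "An intention-to-treat (ITT) and per-protocol analysis is planned"; "Baseline characteristics will be assessed to identify any differences between treatment groups that would require adjustment in subsequent analyses"; "All tests will be two-tailed and assessed at the 5% alpha level".
- **Procedures**: "Participants will undergo assessments at base line, 3 weeks, 3 months and 5 months following the injection", and "All primary and secondary outcomes will be measured at all 4 time points". This gives three post-injection visits.
- **Outcomes**: the primary and secondary outcomes are defined as changes.
- **Sample size calculation**: a difference of 0.13 with standard deviation 0.13, 90% power, a design effect of 1.5, and a final inflation to 47 per group "to account for an expected attrition rate of 25"%.

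**The concern.** With two arms and three post-injection visits, an overall model test does not say at which visit the arms differ or by how much. A pairwise step normally answers that, and the article gives this step to a simpler method than the one just fitted. Three things follow if these are ordinary t-tests on the data of a visit.

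1. Patients who left before the visit drop out of the comparison, although the model would use their earlier visits. This sits badly with an intention-to-treat aim and a quarter of patients expected to be lost.
2. A t-test has no covariates, so any baseline adjustment judged necessary stops short of these comparisons.
3. The t-test and the model can give visibly different differences at the same visit, with no rule for which one is believed.

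At stake are precision, possible bias and consistency of the visit-specific results.

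**Working it through.** **Inputs.** From the article: 47 per arm, standard deviation (SD) 0.13, difference 0.13, 25% attrition. The within-patient correlation (rho) and the dropout mechanism are not given. They are assumed here, and ranges are shown.

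**The plan's own figure.** A two-sided 5% t-test with 90% power at 0.13/0.13 = 1.0 SD needs 22.02, so 23 per arm. 23 × 1.5 = 34.5, so 35. 35/0.75 = 46.7, so 47. The stated 23, 35 and 47 are reproduced and are not disputed.

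**Patients in a 5-month t-test.** 47 × 0.75 = 35.25, so about 35 per arm, or 70 of 94.

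**Standard error (SE) with 35 per arm.**

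- t-test on raw values: 0.13 × √(2/35) = 0.0311.
- t-test on change: 0.0311 × √(2(1 − rho)).
- Baseline-adjusted: 0.0311 × √(1 − rho²).

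| Assumed rho | Raw values | Change | Baseline-adjusted |
|---|---|---|---|
| 0.5 | 0.031 | 0.031 | 0.027 |
| 0.7 | 0.031 | 0.024 | 0.022 |
| 0.85 | 0.031 | 0.017 | 0.016 |
| 0.9 | 0.031 | 0.014 | 0.014 |

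The ratio of adjusted to change-score SE is √((1 + rho)/2): 0.87, 0.92, 0.96 and 0.97 down the table. Simulation of a likelihood-type estimate that also uses dropouts' earlier visits gave nearly the same model SEs: 0.027, 0.022, 0.016 and 0.013. Most of the gain in precision therefore comes from the baseline term.

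**Disagreement between the two estimates.** If the model estimate is efficient, the variance of the gap is the difference of the two variances. At rho 0.7 the SD of the gap is √(0.0311² − 0.0222²) = 0.022 for raw values and √(0.0241² − 0.0222²) = 0.009 for change. In simulation with the same dropout rule in both arms, the raw-value t-test and the model differed by more than 0.02 in 21% to 46% of trials (rho 0.5 to 0.9). Those percentages apply to raw values; the gap is clearly smaller for change scores.

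**Bias under assumed dropout.**

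- *Change scores.* Loss after 3 weeks depends on poor 3-week response, giving about 15% loss on botulinum toxin and 35% on placebo. The t-test averages 0.122 and the model 0.130. Shortfall: (0.130 − 0.122)/0.130 = 6%.
- *Raw values, arm-dependent rule.* Loss depends on the previous value in the placebo arm only. With no true effect, the t-test is off by −0.021, −0.029 and −0.035 at rho 0.5, 0.7 and 0.9, and rejects in 10%, 16% and 19% of trials. With a true effect of 0.13 it averages 0.109, 0.102 and 0.095. The model-type estimate stays at about 0 and 0.130.
- *Raw values, same rule in both arms.* With no true effect there is no bias, and rejection is about 5%. With a true effect of 0.13 the t-test averages 0.126, 0.125 and 0.123, because the effect itself makes losses unequal.

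**Power.** At a difference of 1.0 SD, 35 completers per arm give the plain t-test 98% power.

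**The case against.** The strongest reply has four parts.

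*The treatment effect stays with the model.* This stands. A reader might infer that the plan abandons the model at the step that yields the treatment effect. The text does not say so: the t-test is named only for post hoc pairwise comparisons. Nor does it say that these are between-arm tests at each visit; that is the natural reading, not a stated one. An overall model test and a visit-specific test also answer different questions, so two p-values for one question are not established.

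*The wording may be shorthand for model contrasts, which are themselves t-tests.* This is possible, and an analysis plan that is not shown may say so. But the article names a test without that qualification. If contrasts were meant, the same replacement sentence states it.

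*Outcomes are defined as changes, so baseline is not ignored.* This largely stands. A change-score t-test subtracts baseline, and the claim that baseline is ignored holds only for raw values. Subtraction is still not adjustment, and other covariates found to need adjustment would be left out.

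*The bias rests on invented dropout.* This stands as a limit. The article gives no mechanism.

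Two further inferences fail. One is that the t-test is the stated tool for the ordinal Modified Ashworth Scale; no test is assigned to that scale, and a linear mixed model would raise the same question. The other is that visit-to-visit comparisons within an arm would be invalid; that would be so only for the independent-samples form, and a paired form exists.

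**Conclusion.** The point holds in a limited form. The article names a weaker method for the pairwise comparisons than the model it has already planned. If these are arm comparisons at a visit, they omit about a quarter of patients at 5 months, cannot carry the foreseen adjustment and may disagree with the model.

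The cost depends on what is tested. Across assumed correlations of 0.5 to 0.9, change-score tests have SEs that the model would cut by about 13% down to 3%. Raw-value tests lose more as the correlation rises. Bias relative to the model needs loss that is both unequal by arm and related to earlier response. If loss depends on unobserved values, the model is not protected either. The sample size and its power are unaffected. This is a correction worth making, not a threat to the main analysis.

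**What to change.** Replace the t-test sentence with:

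*Between-arm differences at each post-injection visit will be estimated as treatment-by-visit contrasts with 95% confidence intervals from the linear mixed model, with visit categorical, unstructured within-patient covariance, and the baseline value handled in the model (for example as part of the outcome vector with a common baseline mean, so that all randomised patients contribute).*

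The baseline term must be named, since most of the gain in precision comes from it. Placing baseline in the outcome vector also keeps patients with no post-injection value, in line with the intention-to-treat aim. Any comparison of visits within an arm should likewise be a model contrast.

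The cost is one sentence. The model is already planned, and no extra patients, visits or data are needed.

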### Cost benefit analysis

To inform the economic evaluation of Botulinum toxin for post stroke spasticity, differences in quality of life will be assessed between the intervention and control group. There are potential spillover effects of improving patients’ quality of life on the quality of life of patients’ carers. Both patients and carers will be asked to complete the 12 question, SF12 survey at every clinic visit. These data can be converted to utility values to inform the estimation of quality adjusted life years (QALYs).

The cost data included in the economic evaluation will focus on costs incurred in public hospitals, as this patient group are unlikely to make significant use of private hospitals. Patients will be asked for consent to access identified cost and activity data through SA Health. Patients and their carers will also be asked to describe their use of primary health care services in between clinic visits, to which unit costs will be attached to add to the cost analysis.

On completion of the trial, aggregate cost and QALY estimates will be generated for each patient. Differences in mean costs and QALYs will be used to generate the expected incremental cost per QALY gained. Bootstrapping will be used to represent the uncertainty around the mean result.

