This study will provide useful descriptive information relating to spasticity and its effects following stroke qualitatively and quantitatively. The study will then also provide information on the ability of BT to control spasticity in order to retrain participants walking ability, outcomes on activities of daily living and quality of life. Given a positive study result in improving lower limb function it will provide an evidence-based treatment option that can argue for changes in PBS policy in funding the use of BT for treatment of PSLLS.

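### Incremental QALYs are set as a difference in arm means with no adjustment for baseline utility, although baseline SF-12 is collected: unbiased, but needlessly imprecise

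*Protocol article*

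**What the plan says.** The Cost benefit analysis section obtains utilities from SF-12: "Both patients and carers will be asked to complete the 12 question, SF12 survey at every clinic visit". It then says that "aggregate cost and QALY estimates will be generated for each patient", and the economic contrast follows: "Differences in mean costs and QALYs will be used to generate the expected incremental cost per QALY gained". On uncertainty it says "Bootstrapping will be used to represent the uncertainty around the mean result". No covariate is named anywhere in the section.

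The Procedures section gives the schedule: "Participants will undergo assessments at base line, 3 weeks, 3 months and 5 months following the injection". It adds that "All primary and secondary outcomes will be measured at all 4 time points". SF-12 is listed among the secondary outcomes, so a baseline value is planned for every patient.

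Two other places bear on the point. Under Consent and randomization, stroke type is the only stratifier. Under Statistical methods there is one general sentence on adjustment: "Baseline characteristics will be assessed to identify any differences between treatment groups that would require adjustment in subsequent analyses".

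**The concern.** A QALY total accumulated from baseline contains baseline utility twice: directly, in the first interval, and indirectly, because patients who start higher tend to stay higher. Baseline utility is not a stratifier, so the arms are balanced on it only by chance, with 35 evaluable patients per arm. A plain difference in mean QALYs carries that chance gap into the denominator of the cost per QALY. Over five months the denominator will be small in any case.

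At stake is the precision of the incremental QALY estimate and of any ratio built on it. The Discussion says that a positive result on lower limb function could be used to "argue for changes in PBS policy in funding the use of BT for treatment of PSLLS", so the economic result has a policy readership.

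**Working it through.** **The plan's own figures.** The article gives no utility or QALY figure. Its sample size supplies the number per arm and can be reproduced. For a difference of 0.13, SD 0.13, two-sided 5% and 90% power, the two-sample t-test needs 23 per group (power 0.912; 22 falls just short). Then 23 × 1.5 = 34.5, so 35, and 35 / 0.75 = 46.7, so 47.

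**Assumptions, not in the article.** QALY taken as the trapezoid area under the utility curve; utility SD 0.10 to 0.15, equal at all visits; the same correlation ρ between any two visits, 0.3 to 0.7; utility gain 0.02 to 0.05, sustained from week 3 to month 5.

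**Weights.** Visits at 0, 3/52, 0.25 and 5/12 year give trapezoid weights 0.029, 0.125, 0.179 and 0.083. They sum to 0.417; the three follow-up weights sum to 0.388. Their squares sum to 0.0556 (all four) and 0.0548 (follow-up only).

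**Precision.** Per unit SD² × 2/n, the variance of the QALY difference is
- unadjusted: (1 − ρ) × 0.0556 + ρ × 0.417²
- adjusted for baseline utility: (1 − ρ) × 0.0548 + ρ(1 − ρ) × 0.388²

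| ρ | unadjusted | adjusted | variance ratio | SE reduction |
|---|---|---|---|---|
| 0.3 | 0.0910 | 0.0699 | 0.77 | 12% |
| 0.5 | 0.1146 | 0.0650 | 0.57 | 25% |
| 0.6 | 0.1264 | 0.0580 | 0.46 | 32% |
| 0.7 | 0.1382 | 0.0480 | 0.35 | 41% |

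The reduction does not depend on the SD, the gain or n. At ρ = 0.5 to 0.7 it is worth as much QALY precision as raising 35 per arm to about 62 (35 / 0.567) to 101 (35 / 0.347). For scale, at SD 0.12 and 35 per arm the SE falls from 0.0097 to 0.0073 (ρ = 0.5) or from 0.0107 to 0.0063 (ρ = 0.7).

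**Carry-over of a chance gap.** The SE of the baseline gap is SD × √(2/35): 0.024 at SD 0.10 and 0.036 at SD 0.15. The shift in the QALY difference is the gap × (0.029 + ρ × 0.388).
- SD 0.10, ρ = 0.5: 0.0239 × 0.223 = 0.0053
- SD 0.15, ρ = 0.7: 0.0359 × 0.300 = 0.0108

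**Against the gain.** A sustained gain is worth gain × 0.388. The chance that the carried-over gap is at least that large, in either direction, is 2 × [1 − Φ(gain QALY / one-SE shift)]. The low end uses a shift of 0.0053, the high end 0.0108.

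| Utility gain | QALY | Chance that the gap matches it |
|---|---|---|
| 0.02 | 0.0078 | 15 to 47% |
| 0.03 | 0.0116 | 3 to 28% |
| 0.04 | 0.0155 | under 1 to 15% |
| 0.05 | 0.0194 | under 1 to 7% |

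**The case against.** The strongest reply has four parts.

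- **The text does not say unadjusted.** A regression-adjusted contrast is also a difference in means, and the Statistical methods sentence on baseline differences might be read to cover the economic analysis. It is right that the word is absent; reading the contrast as raw is an inference from the lack of any named covariate. But the general sentence acts only when an imbalance is judged to need it, and it names neither utility nor the economic evaluation. Even if it applied, it would leave the estimator to be chosen after seeing the data and would give up the precision gain whenever no imbalance was flagged.
- **No validity error.** This stands. Under randomization the unadjusted difference is unbiased, and the bootstrap reports its sampling noise honestly, which is all that the article claims for it. A reader might infer systematic bias or a faulty bootstrap; the documents support neither.
- **The size is assumed.** This stands for the comparison with the gain, which weakens quickly as the gain rises. It bears less on the relative SE reduction, which needs only the correlation structure, and that is shown down to 0.3.
- **A condensed article leaves model detail to a fuller plan.** A health economic plan may well adjust. If so, the article's stated contrast needs only one clause to agree with it.

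**Conclusion.** The point holds as a free improvement, not as an error of validity. The article states the QALY contrast without a baseline-utility term, and a more precise estimator is available from data already planned. The gain is a 12 to 41% smaller SE for the QALY difference at an equal between-visit correlation of 0.3 to 0.7. A chance gap as large as the treatment gain is realistic if that gain is 0.02 to 0.03 in utility and unlikely near 0.05; the SD, correlation and gain are all assumptions.

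Two stronger readings are not supported. One is that a chance gap is likely to double the cost per QALY or reverse its sign. For a gain of 0.03, reversal through carry-over alone needs an adverse gap of 0.0116 / 0.0108 = 1.1 to 0.0116 / 0.0053 = 2.2 standard errors, a one-sided chance of about 14% down to 1%. Nor would adjustment make the ratio stable: the adjusted SE of 0.0063 to 0.0073 at SD 0.12 is still more than half of 0.0116. The other is that the reimbursement case rests on this ratio. The Discussion ties it to a positive result on lower limb function, and the Abstract describes the barrier as weak evidence on walking and quality of life.

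**What to change.** In the Cost benefit analysis section, state that incremental QALYs will be estimated by regressing each patient's area-under-the-curve QALY on treatment, baseline SF-12 utility and stroke type (included because it is the randomization stratifier), whether or not a baseline imbalance is observed. State that patient-level pairs of cost and QALY will be bootstrapped within arm and the regression refitted in each resample, so that the uncertainty reported belongs to the adjusted estimate.

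The cost is a few lines of analysis wording. Baseline SF-12 and stroke type are already collected, so no new data, visits or patients are needed. If a separate health economic plan already specifies this, a single clause referring to it is enough.
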